## 5. Analysis

**5.1 Diagnostic Performance Study:** A cross tabulation of IDx-DR results (positive, negative, ungradable) with the results from the reference standard (positive, negative, ungradable) will be presented for the overall sample. The point estimate for each test characteristic will be presented along with the counts of eyes (numerator and denominator) that contribute to the calculation. One-sided 97.5% confidence intervals will be computed by the cluster bootstrap approach to account for correlation introduced by taking measurements from both eyes of each subject; in cases where the confidence interval is not estimable using the cluster bootstrap approach due to small sample sizes or boundary values (e.g., a test characteristic of 100%), the exact binomial confidence interval will be presented instead. Primary endpoints will be reported in stratified

[figure not shown]

|                     |               |        |              |
|---------------------|---------------|--------|--------------|
| CTMF-SA-DXSDR006-03 | SAP_2.1_clean | Rev. A | Pg. 10 of 16 |
|---------------------|---------------|--------|--------------|

analyses by eye, age, sex, and race/ethnicity. Should enrichment be implemented, further stratification of all endpoints will be presented by cohort: sequential enrollment or enrichment.

The sensitivity, PPV, and NPV analyses will be repeated in the same manner for the weighted samples. The PPV and NPV calculations will be performed using the accrued specificity data without any resampling of eyes with ETDRS level less than 53.

Relevant data analyses will be repeated at the subject-level for regulatory submission and publication consistent with the de novo study utilizing the Topcon NW400 retinal camera.

Data analysis will be performed using SAS (V9.3 or later).

**Population:** We anticipate those recruited will mirror the spectrum of disease severity encountered at primary care settings and be similar to the study population in the pivotal trial. [10] In the analyzable population, 30.9% were  $\geq 65$  years old, 16.4% were Hispanic, 28.2% Black, and 86.7% had HbA1c  $\geq 7$ .

**Protocol deviations:** The contract research organization (Labcorp) will track the progress of subject enrollment and data management, calculating totals per stratum on a monthly basis. While all efforts will be made to minimize the likelihood of protocol deviations through site training on all procedures, potential deviations will be monitored throughout the study. A non-exhaustive list of potential deviations includes:

- failure to obtain signed informed consent before initiating study-related procedures
- an operator taking more than 6 attempts per eye
- an operator failing to take at least 6 attempts without a diagnostic result.

Some protocol deviations may result in participant data excluded from endpoint analysis, while others may not require exclusion of the participant data. Hypothesized deviations and intended actions are described in **Supplementary Table 5**, and any new deviations will similarly be outlined with an action plan prior to formal statistical analysis.

#### Supplementary Table 5: Protocol deviations

| Deviation                                                                            | Action                                                                                                                   |
|--------------------------------------------------------------------------------------|--------------------------------------------------------------------------------------------------------------------------|
| Failure to obtain signed informed consent before initiating study-related procedures | Exclude participant data from endpoint analysis                                                                          |
| More than 6 attempts per eye                                                         | Only data from the first 6 attempts may be included in endpoint analysis (exclude attempt 7 or greater)                  |
| Failing to make at least 6 attempts without a diagnostic result                      | Exclude participant data from endpoint analysis                                                                          |
| Failure to capture both eyes for a participant                                       | The single eye may be included should no other protocol deviations be associated with the participant's data collection. |

[figure not shown]

|                                                                 |               |                                                 |              |
|-----------------------------------------------------------------|---------------|-------------------------------------------------|--------------|
| CTMF-SA-DXSDR006-03                                             | SAP_2.1_clean | Rev. A                                          | Pg. 11 of 16 |
| After enrollment, an eligibility criterion not met per protocol |               | Exclude participant data from endpoint analysis |              |

In all cases of protocol deviations, the site will be notified of the deviation to prevent future such occurrences. The final analytic sample size for primary endpoints will be described with counts and reasons for exclusion (protocol deviations, reading center ungradable, or IDx-DR ungradable) in a flow diagram as in **Figure 1**.

Figure 1: Example flow diagram

[figure not shown]

**Baseline Covariates:** Data collection for each eye will include a unique participant identifier plus age in years at exam, sex, race, ethnicity, ocular condition/procedure history, non-ocular comorbid conditions, diabetic status including duration of diagnosis, recent lab tests (HbA1c, fasting glucose). Continuous variables will be summarized using descriptive statistics (means, standard deviations, and quartiles), and nominal variables will be summarized using counts and percentages. Primary endpoints may be reported in stratified analyses by age, sex, and race/ethnicity. Demographic variables will be presented at the subject-level and eye-level according to: (1) not mtmDR or vtDR, (2) mtmDR, and (3) vtDR.

For the weighted sampling, the demographics (means, SDs) will also be repeated to include those subjects with eyes selected from overweight sampling.

**Missing Data:** By design, each eye will be represented in a cell in the crosstabulation depicted in Section 2.3; missing data are not anticipated. Any missing or ungradable data will be displayed; all available eye-level data will be used. The primary endpoints will be assessed where both the PRS and IDx-DR results will be gradable. Secondary “worst case scenario” analysis considers ungradable values within the calculation.

**Statistical Analysis:** A cross-tabulation of IDx-DR results (positive, negative, ungradable) with the results from the reference standard (positive, negative, ungradable) will be presented for the overall sample. The point estimate for each test characteristic will be presented along with the counts of eyes (numerator and denominator) that contribute to the calculation. Should enrichment be implemented, further stratification will report point estimates and counts of eyes (numerator and denominator) by cohort (not enriched, enriched).

Eye-level one-sided 97.5% lower confidence intervals will be computed by the cluster bootstrap approach to account for correlation introduced by taking measurements from both eyes of each subject [12]; specifically:

[figure not shown]

|                     |               |        |              |
|---------------------|---------------|--------|--------------|
| CTMF-SA-DXSDR006-03 | SAP_2.1_clean | Rev. A | Pg. 12 of 16 |
|---------------------|---------------|--------|--------------|

- participants will be stratified by the number of eyes contributing to the analysis (1 or 2) and by the number of eyes with mtmDR(+) (0, 1, or 2)
- sampling with replacement will be performed within each stratum until the same number of participants per stratum are selected
- all eligible eyes per participant selected in the bootstrap sample will be included to estimate the point estimate in the bootstrapped sample
- this process will be repeated 1000 times, with the empirical 95% confidence interval reported as the 25th and 975th ordered point estimate from bootstrapped samples
- in case the confidence interval is not estimable using the cluster bootstrap approach due to small sample sizes or boundary values (e.g., a test characteristic of 100%), the exact binomial confidence interval will be presented instead.
- Weighted sampling will also be conducted to assess the impact of prevalence upon sensitivity, PPV, and NPV. This is important to ensure that these outcomes can be extrapolated to populations with higher proportions of eyes with ETDRS level at least 53.

In addition, eye-level logistic regression models will be performed to account for correlations and the same baseline covariates. The model-based estimates will be corrected to address the estimate bias introduced by using logs introduced by logistic regression.

Relevant data analyses will be repeated at the subject-level for regulatory submission and publication consistent with the de novo study utilizing the Topcon NW400 retinal camera.

**Reporting:** The CONSORT-AI [Consolidated Standards of Reporting Trials–Artificial Intelligence] extension to the 2010 CONSORT statement provides guidelines for reporting interventions involving artificial intelligence [13]. The 25 item CONSORT 2010 checklist includes 14 new items with additional detail about the AI component. The checklist will be completed by the study statistician with input from the study sponsor and will be included in any publication resulting from this trial.

**5.2 Precision Substudy:** The repeatability and reproducibility substudy will be performed including three cameras and three operators (see Section 3.2). A Latin Squares design (Supplementary Table 6) will be used with mixed effects models used to analyze the DDx algorithm outcome data on a log-scale with operator, camera, sequence, dilation, and FPRC as covariates. Separate analyses will be performed at the subject-level and at the eye-level. Each of 36 subjects, 50% positive for mtmDR in at least one eye, will have a total of 9 results on each eye (see protocol Section 9.4.1). Repeatability will be assessed within the three replicates from pre-specified camera-operator pairs, and reproducibility will be assessed from comparing results across the six camera-operator combinations. There will be 3 replicates on all 36 subjects (72 eyes) for 216 gradings for the replicate analyses and 6 measures on all 36 subjects (72 eyes) for 432 gradings for the reproducibility analysis.

[figure not shown]

|                     |               |        |              |
|---------------------|---------------|--------|--------------|
| CTMF-SA-DXSDR006-03 | SAP_2.1_clean | Rev. A | Pg. 13 of 16 |
|---------------------|---------------|--------|--------------|

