| $d_1 = 0.085$ is the difference at which power is calculated. $d_1 = p_1 - p_0$ and is the hypothesized sensitivity value above the non-inferiority threshold                         | $d_1 = 0.096$ is the difference at which power is calculated. $d_1 = p_1 - p_0$ and is the hypothesized specificity value above the non-inferiority threshold                         |        |             |
| n=200 mtmDR(+) eyes                                                                                                                                                                   | n=140 mtmDR(-) eyes                                                                                                                                                                   |        |             |
| Reject $H_0$ for at least 163/200 true positive eyes, or at least 81.2% sensitivity.
Establish superiority for at least 172/200 true positive eyes, or at least 85.7% sensitivity. | Reject $H_0$ for at least 119/140 true negative eyes, or at least 84.6% specificity.
Establish superiority for at least 122/140 true-negative eyes, or at least 86.7% specificity. |        |             |

The mtmDR(+) and mtmDR(-) sample size depends on the WRC findings so the study will enroll to a target of 564 eyes (282 subjects maximum) to ensure sufficient numbers for the sensitivity and specificity analyses. In addition, in order to achieve 200 mtmDR(+) eyes, we anticipate >450 mtmDR(-) eyes will be accrued based on the historical enrollment ratio (1:4). Thus, the specificity power will be increased and the threshold to establish non-inferiority and superiority will be reduced. Similarly, in the event that >200 mtmDR(+) eyes are determined, all eyes will be included. Thus, the plan is to include all recruited subjects in the final analyses in support of the intent to diagnose analysis principle.

Additionally, weighted sampling will be performed by sampling with replacement among eyes with ETDRS levels at least 53 for computing sensitivity, PPV, and NPV in settings with higher prevalence of severe disease. The overweight sampling is expected to achieve similar sensitivity due to the samples being drawn at random from the gradable and sufficient eyes with ETDRS greater than 53. This analysis is being done following discussion with FDA to assess PPV and NPV outcomes in populations with different vision threatening incidence.

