### **5.9. Off Study/End of Study Definition**

#### **5.9.1. Off Study**

Subjects will be considered Off Study at the time of withdrawal of full consent, once they have completed the study, or at the End of Study (defined below). Subjects will also be taken Off Study due to any of the following:

- If at any time in the study, dilation is deemed to be contraindicated for the subject.
- If subject is non-compliant with study visits or study procedures.
- Investigator determines that continuing on study is not in the best interest of the subject.

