of “Exam Quality Insufficient” for either eye, the subject’s eyes will be dilated. The subject will first be asked to remove contact lenses if they are wearing contacts. Tropicamide 1% eye drops will be administered by qualified site staff under medical supervision. The subject will then be asked to wait at least 30 minutes or until the pupils are dilated to at least 5 mm. The operator will then attempt to image and submit images again. If after a further three attempts a diagnostic result is still not received, no further imaging attempts will be executed, PRS and the IDx-DR output for that/those eye(s) will be recorded as “Exam Quality Insufficient”. After the RV700 Imaging and AI Procedure is complete, subjects will advance to the PRS imaging protocol, the 4Widefield stereo & macular OCT Imaging Procedure performed by a FPRC certified ophthalmic photographer. The FPRC certified photographer will use a different, FDA-cleared camera system for widefield stereo color fundus photography as well as macular Spectral Optical Coherence Tomography (OCT) capability to perform dilated 4W four-field fundus photography and macular (OCT) imaging for each eye. Following the capture of the 4W and OCT images, the subject’s participation in the Diagnostic Performance main study will be complete.

After completion of the Diagnostic Performance Study, RV700, 4W and OCT images from each eye will be passed to retinal grading experts at a qualified reading center, who will independently determine the prognostic reference standard (PRS) for each eye from the 4W & OCT images, and ICDR grading from the RV700 images, and will be masked to each other and the IDx-DR diagnostic output. If the image is insufficient in any way, the ophthalmologist can record a determination of “ungradable”.

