## 9. Statistical Considerations

### 9.1. Hypothesis testing

In this study a minimum of 200 eyes with mtmDR and at least 140 eyes without mtmDR will be enrolled in the main diagnostic performance study. The device performance will be evaluated per eye. The primary endpoints will be sensitivity and specificity of IDx-DR paired with the RV700 in detecting mtmDR based on eye-level results when compared to a PRS by three retinal experts. Intent-to-treat (ITT) analyses are planned; supportive analyses are planned (see Statistical Analysis Plan [SAP] table shells).

As this study is intended to support an extension of the IDx-DR labeling to validate a new camera model for use with IDx-DR, the performance is expected to be substantially equivalent to the predicate device. Substantial equivalence will be assessed as non-inferiority since higher than expected performance is a favorable outcome. The non-inferiority targets will be set based on Sponsor expectations for eye-level sensitivity and specificity. Published results of this trial and NW400 subject-level estimates are summarized in [Supplementary Table 7](#)

**Supplemental Table 7:** Eye-level diagnostic design parameters and pivotal study subject-level performance

|             | Eye-level
Null Hypothesis
$p_0$ | Subject-level
Point Estimate
(two-sided 95% CI) |
|-------------|---------------------------------------|-------------------------------------------------------|
| Sensitivity | 75.0%                                 | 87.2% (81.8%-91.2%)                                   |
| Specificity | 77.5%                                 | 90.7% (88.3%-92.7%)                                   |

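### The short-exam exclusion in SAP Supplementary Table 5 is triggered only by IDx-DR non-results, removes both eyes, and generally raises diagnosability and worst-case accuracy

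*Combined protocol and SAP*

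**What the plan says.** SAP 5.1, Supplementary Table 5, pairs the deviation "Failing to make at least 6 attempts without a diagnostic result" with the action "Exclude participant data from endpoint analysis". The sensible reading is that an eye ended with no result and fewer than six attempts had been made. The action applies to the participant, so both eyes go, and it names no particular endpoint.

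Another row of the same table treats an eye that was not captured more leniently: "The single eye may be included should no other protocol deviations be associated with the participant's data collection". The table does not say how the two rows are told apart when few attempts were made.

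Protocol 7.5 sets the full procedure at three attempts, dilation, then three more: "If after a further three attempts a diagnostic result is still not received, no further imaging attempts will be executed". Only then is the eye recorded as insufficient.

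Other parts of the plan point towards keeping everyone:
- SAP 4: "Thus, the plan is to include all recruited subjects in the final analyses in support of the intent to diagnose analysis principle".
- SAP 5.1, Missing Data: "By design, each eye will be represented in a cell in the crosstabulation depicted in Section 2.3; missing data are not anticipated". The same paragraph commits to using whatever eye-level data are available.
- Protocol 9.1: "Intent-to-treat (ITT) analyses are planned".

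**The concern.** An eye that gets a result on any attempt from one to five can never trigger the rule. Exclusion therefore depends on what the index test returned. Two secondary endpoints exist to describe eyes without a result: diagnosability, and the analysis that counts such eyes as false negatives or false positives. Removing some of those eyes by rule weakens both, and the worst case is then no longer the worst case. The fellow eye is lost too, even when it has a valid result that belongs in the primary endpoints.

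**Working it through.** **The plan's own figures.** The SAP gives no expected diagnosability, ungradable rate or short-exam rate, so there is no figure on this point to reproduce. Its stated 80% power does reproduce with the exact binomial: P(X ≥ 163 | n = 200, p = 0.835) = 80.6% for sensitivity and P(X ≥ 119 | n = 140, p = 0.871) = 80.9% for specificity. The exclusion rule plays no part in that calculation.

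**Formulas (SAP 2.3).** Diagnosability = (PP+PN+NP+NN)/(TP+TN). Worst-case sensitivity = PP/(PP+NP+UP). Worst-case specificity = NN/(PN+NN+UN).

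**Direction.** If both eyes have a gradable PRS, the deleted participant contributes 0 or 1 diagnosed eyes out of 2. Deletion therefore raises diagnosability whenever the overall rate exceeds 50%.

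**Diagnosability.** N = 564 eyes (282 subjects) is the SAP 4 target. Assumptions: all eyes PRS-gradable; U other ungradable eyes; F affected subjects, each with one failed eye and a diagnosed fellow eye.

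Kept = (N − U − F)/N. Deleted = (N − 2F − U)/(N − 2F).

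With U = 28 (about 5%):

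| F | Kept | Deleted | Rise (points) |
|---|---|---|---|
| 3 | 533/564 = 94.5% | 530/558 = 95.0% | 0.5 |
| 6 | 530/564 = 94.0% | 524/552 = 94.9% | 1.0 |
| 14 | 522/564 = 92.6% | 508/536 = 94.8% | 2.2 |

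Over U = 0 to 56 and F = 3 to 14 the rise is 0.4 to 2.5 points. If both eyes of each affected subject fail, it is 1.0 to 5.0 points.

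**Worst-case sensitivity.** From the SAP: 200 mtmDR(+) eyes and the hypothesised sensitivity of 83.5%. Assumptions: 10 other ungradable eyes and 6 short-exam eyes.
- Kept: 0.835 × 184 = 153.64 detected; 153.64/200 = 76.8%.
- Deleted, fellow eyes mtmDR(+) and detected at the same rate: (153.64 − 5.01)/188 = 79.1%.
- Deleted, every fellow eye a true positive: (153.64 − 6)/188 = 78.5%.
- Deleted, fellow eyes mtmDR(−): 153.64/194 = 79.2%.

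**Discordant pairs.** Take 140 mtmDR(−) eyes with 122 true negatives (87.1%, the hypothesised specificity). Suppose the six failed eyes are mtmDR(+) and their fellow eyes are true negatives. Worst-case specificity then goes from 122/140 = 87.1% to 116/134 = 86.6%, a small fall.

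**If the exam had been completed.** Let q be the share of short-exam eyes that would have obtained a result in the remaining attempts. Setting (N − U − F + Fq)/N equal to the deleted value gives 1 − q = 2U/(N − 2F). For U = 28, F = 6: 56/552 = 0.10, so q = 90%. For U = 56, F = 14: 112/536 = 0.21, so q = 79%. For U = 0, q = 100%. Against a completed exam, the upward shift disappears only if roughly 79 to 100% of these eyes would later have succeeded.

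**Primary endpoints.** These already leave out ungradable eyes, so the failed eye does not enter them either way. What is lost is the fellow eye: 3 to 14 eyes in the illustration. If those eyes are classified correctly at the same rate as the rest, precision is lost but the estimate does not shift.

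**The case against.** A reader might infer that the rule deletes only device failures and biases every measure upward. It does not: valid fellow eyes go too, and the discordant-pair example shows worst-case specificity falling.

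A reader might also treat a short exam as a device failure. The documents call it an operator deviation (SAP 5.1) and record insufficiency only after six attempts, so it is an incomplete exam. Counting it as a non-result is a choice of estimand, though one in keeping with an analysis labelled worst case.

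Some short exams could not enter UP or UN at all. PRS imaging comes after the RV700 procedure and is dilated, and one ground for going off study is "If at any time in the study, dilation is deemed to be contraindicated for the subject". Such a subject would probably have no PRS, and would be in none of these denominators. This stands, and the fix must allow for it.

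The conflict with other sections can be read more softly. The SAP 4 sentence closes a paragraph about keeping eyes beyond the minimum numbers, and the ITT sentence points to SAP table shells not available here, which might restore these participants. The SAP 4 sentence is nevertheless worded for every recruited subject, and the Missing Data paragraph gives each eye a cell. The promised flow diagram would disclose counts and reasons for the primary endpoints, but disclosure does not put the eyes back.

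Finally, a reader might infer that study success is at risk. The exact lower bound is 75.4% for 163/200 and 74.99% for 163/201, so one restored eye appears decisive. But the 75% criterion belongs to primary sensitivity, which omits ungradable eyes. The worst-case analysis has no stated threshold.

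**Conclusion.** The point holds in a limited form. The exclusion depends on the index-test result and conflicts with the intent-to-diagnose and missing-data statements. For participants with a gradable PRS, it generally favours diagnosability and the worst-case measure for the failed eye's PRS class, relative to counting that eye as a non-result. It bears mainly on secondary endpoints and reaches the primary ones only through discarded fellow eyes.

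The size cannot be fixed from the documents. The range of about 0.4 to 2.5 points in diagnosability rests on assumed counts: 3 to 14 affected subjects of 282, one failed eye each, and 0 to 56 other ungradable eyes. With no such deviations the effect is zero. No analysis in the supplied text restores these participants.

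**What to change.** Change the action for this row of Supplementary Table 5 as follows:
- Retain the participant and keep the fellow eye's result.
- Count the short-exam eye as IDx-DR ungradable in the cross-tabulation, diagnosability and worst-case analysis: UP or UN by its PRS, or UU if the PRS is ungradable.
- List eyes with no PRS imaging separately as missing.
- Report the analysis that excludes the participant as a sensitivity analysis only.

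The change is to one table cell and affects analysis only; imaging procedures stay as they are. The cost is that reported diagnosability and worst-case accuracy may be slightly lower, because some incomplete exams then count as failures.
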